## **PROTOCOL**

### **Subject Recruitment**

According to the enrollment schedule, subjects recruited during project year 1 will be followed through project year 3; those recruited during year 2 will be followed through year 4; those recruited during year 3 will be followed through year 5. Over the 5-year study period, we will need to retain 50 subjects to achieve the effect size of 0.80. To reach the desired effect size, we will screen by phone approximately 250 subjects (83 subjects per year). We anticipate that 102 subjects will meet preliminary inclusion criteria and will be scheduled for the initial visit (34 subjects per year) and we expect to randomize approximately 71 subjects who meet full inclusion criteria (24 subjects per year), bearing in mind expected rate for the telephone screening (60%), failure to meet inclusion criteria at initial visit (30%) and attrition due to withdrawal from the study either by the PI or by the subject herself (30%). We estimate a 70% rate of subject inclusion in the current proposal based on: a) growing concern on the side of physicians and women alike of the utility of long-term estrogen use in postmenopause; b) interest in definition of the risk for cognitive decline among postmenopausal women and c), brain imaging procedures (in her previous studies, the PI had encountered sustained interest in participation in the studies involving PET imaging to predict possible AD).

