### **Subject Participation**

In the present study, participants will be randomly assigned to continue or discontinue their existing estrogen hormone therapy (HT) for the duration of the 2-year study. The assessment schedule includes: a) screening and identification of subjects who meet inclusion criteria; b) clinical evaluation and blood drawing for general chemistry and other analyses; c) baseline neuroimaging (MRI, PET) and neuropsychological assessments; d) interim assessments; and e) two-year follow-up assessments. All tests performed at baseline will be repeated at a 2-year follow-up. Interim assessments with subjects in between in-person visits will include telephone contact at least every other month. At each three-month interval subjects will be asked to return for a follow-up visit to evaluate their general well-being, overall functioning, and subjective memory performance. Subjects will also be encouraged to contact the research team as needed.

Psychiatric examination. The baseline psychiatric assessment includes a psychosocial history, Structured Clinical Interview for DSM-IV--Patient Edition (SCID), and mental status examination,

and will take approximately hours to complete. [name] will oversee the clinicians that perform the psychiatric assessments and evaluate interrater reliability.

The following standardized rating scales and questionnaire will be used:

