## **Data Analysis**

PET data will be analyzed by the statistical parametric mapping method of Friston and colleagues [11] to assess the main hypothesis of differences in HT randomization groups. Briefly, images from all subjects will be co-registered and reoriented into a standardized coordinate system using the SPM8 software package courteously provided by the Wellcome Department of Cognitive Neurology, Functional Imaging Laboratory (London). Data will be spatially smoothed, and normalized to mean global activity as previously described [12], except that an 8mm smoothing filter will be applied to images prior to statistical analysis. The set of pooled data will then be assessed with the t-statistic on a voxel-by-voxel basis, to identify the profile of voxels that significantly differed between subject groups. Brain regions considered appropriate for examination a priori, based upon well-established metabolic involvement in the earliest stages of prodromal Alzheimer's disease, are the bilateral precuneus/posterior cingulate areas, parietotemporal cortex in the vicinity of the angular and marginal gyri; medial prefrontal cortex, given its aging-related metabolic decline; and the medial temporal including the hippocampal area, inferior lateral temporal, and dorsolateral prefrontal cortex, for their roles in cognitive processes vulnerable to early decline in aging individuals [13, 14]. To statistically protect against multiple comparisons across the volume of the brain, a Bonferroni-type correction will be applied to twelve (left and right) regions specified by the a priori hypotheses, and group difference in those regions were noted if  $p < 0.05$  after correction; differences in other regions will be described here when  $p < 0.0005$  before adjustment. A number of analyses will be completed after stratifying the subjects according to estrogen HT formulation and various clinical variables, such as presence of APOE-4.

Clinical, demographic, and neuropsychological data will be analyzed using SPSS software version 13.0 (SPSS Inc., Chicago, IL). Two-group t-tests and chi-square tests will be used to assess any potential differences in clinical or demographic variables in the two subject groups (HT continuation or HT discontinuation). Paired t-tests will be used to assess changes in neuropsychological test performance between HT randomization groups to allow for consideration of correspondence with regional cerebral metabolism changes. Significance for

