these analyses will be set at  $p < .05$  level without Bonferonni correction, given the small sample sizes and exploratory nature of these analyses. Further analyses will be conducted to assess differences according to estrogen HT formulation.

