The proposed research will help to define guidelines for estrogen use among postmenopausal women. Specifically, it will provide information regarding the effects of discontinuation from estrogen use on cognitive functioning.

Importance of the Knowledge to be Gained. There is little risk to participating in a study assessing the effects of continuation/discontinuation of estrogen use. Yet there is much to gain from identifying changes in brain metabolism and cognitive function, which may result from discontinuation of estrogen use.

- a) Individual: Subjects will receive a detailed psychiatric, physical, and neurological examination, including laboratory and cognitive assessment, and neuroimaging.
- b) Societal: Results of the study may further understanding of the possible protective effects of estrogen from cognitive decline.

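### The paired t-test named for comparing cognitive change between the randomised groups does not make that comparison, and the protocol names no other between-arm test of cognitive change

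*Protocol*

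**What the plan says.** The Data Analysis section of the protocol gives the test for the cognitive outcomes in one sentence: "Paired t-tests will be used to assess changes in neuropsychological test performance between HT randomization groups". The rest of that sentence says the purpose is to set cognitive changes beside changes in regional brain metabolism.

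The sentence before it names an independent-groups test, but for other variables: "Two-group t-tests and chi-square tests will be used to assess any potential differences in clinical or demographic variables in the two subject groups". Significance for these analyses is 0.05, "level without Bonferonni correction, given the small sample sizes and exploratory nature of these analyses". The PET analysis is a voxel-wise t-statistic between groups, used "to assess the main hypothesis of differences in HT randomization groups".

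On design, the Subject Participation section describes random assignment of each woman to continue or stop her existing therapy for two years. It mentions no matching and no crossover. On measurement, it says: "All tests performed at baseline will be repeated at a 2-year follow-up".

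On aims, the discussion of benefits under Adequacy of Protection Against Risks says of the study that "it will provide information regarding the effects of discontinuation from estrogen use on cognitive functioning".

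**The concern.** A paired t-test needs each value in one set to have a natural partner in the other. Here the only natural pair is the same woman at baseline and at two years. A woman who continues has no partner among those who stop. The test named and the comparison stated therefore do not fit each other.

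If paired tests are run within each arm, the result is two separate statements about change over time and no test of their difference. The sentence's own purpose, a comparison between the groups, could then be met only by setting two p-values side by side. All tests are repeated, so a practice effect could move both arms whatever the treatment. At stake is the protocol's one stated analysis of whether stopping estrogen affects cognition.

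**Working it through.** **Inputs.** 50 women retained and effect size 0.80 (Subject Recruitment); significance level 0.05 without correction (Data Analysis). Assumed, because the protocol does not state them: equal allocation, so 25 completers per arm; two-sided tests; 80% power for the sample-size check; and the size of any change common to both arms. Change is measured in SDs of the change score.

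**The plan's own figure.** The protocol says "we will need to retain 50 subjects to achieve the effect size of 0.80". For a two-sample comparison, n per arm = 2(1.960 + 0.842)² / 0.80² = 2 × 7.849 / 0.64 = 24.5, rounded up to 25, or 50 in all. The figure reproduces. Power with 25 v 25 is 80.7% by the normal approximation and 79.1% by the noncentral t. Attrition also fits: 71 × 0.70 = 49.7. So the sample size is what an independent two-group comparison would need, although the protocol does not say which outcome the 0.80 refers to.

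**Within-arm paired tests when the arms do not differ.** Let both arms have the same true mean change δ. Each paired test has 24 degrees of freedom and noncentrality δ√25 = 5δ; call its chance of significance p. The arms are independent, so the chance that exactly one is significant is 2p(1 − p), computed here from unrounded p.

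| Common change δ (SD) | p in each arm | Exactly one arm significant |
|---|---|---|
| 0 | 0.050 | 9.5% |
| 0.2 | 0.161 | 26.9% |
| 0.3 | 0.302 | 42.2% |
| 0.4 | 0.484 | 49.9% |
| 0.5 | 0.670 | 44.2% |
| 0.6 | 0.821 | 29.4% |
| 0.8 | 0.970 | 5.9% |

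Simulation (50,000 trials per setting) agrees: 9.6%, 27.0%, 50.3% and 29.3% at 0, 0.2, 0.4 and 0.6 SD. In the same trials a two-sample t-test on change was significant in 5.0%, 5.1%, 5.0% and 5.1%. Unequal completion changes little: with 30 and 20 completers the closed form gives 9.5% at 0, 42.7% at 0.3, 51.3% at 0.4 and 46.7% at 0.5.

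**Other ways to carry out the sentence.**
- One paired test over all 50 women tests common change, not the effect of randomisation. With no arm difference it was significant in 4.9%, 28.6%, 79.5% and 98.6% of trials at 0, 0.2, 0.4 and 0.6 SD.
- Pairing women arbitrarily across arms kept the false-positive rate at 5.0% to 5.2%. It is undefined for unequal arms and loses a little power (77.9% against 79.4% at a true difference of 0.80).

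**A real difference of 0.80 SD.** If the arms change by +0.4 and −0.4, exactly one is significant in 49.7% of trials, against 79.4% for the two-sample test. If they change by 0.8 and 0, the figures are 92.3% and 79.1%. The one-arm reading thus depends on where the arms sit relative to zero change as well as on the difference between them.

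**The case against.** The strongest reply is that the harm depends on steps the protocol does not take. A reader might infer that the effect of stopping estrogen will be judged by whether one arm changes significantly and the other does not. No such rule is stated. The words about a comparison between groups may equally mean a two-sample test on change scores that was misnamed, in which case only the label is wrong. Literal pairing across arms would also leave the error rate near 5%. It cannot be said that the plan as written produces false claims, only that it can. This stands.

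The inflation also depends on an assumed common change. The protocol gives no expected change or practice effect. Showing only the middle of the range would mislead, because at 0.8 SD the rate is back to about 6%. This stands too.

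A reader might further infer that the trial's main result is compromised. It is not: the main hypothesis is tested on PET by a between-group statistic, and the cognitive tests are called exploratory. Nor is the absence of an estimate with an interval an error here, since a SAP commonly supplies that.

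What the reply does not remove is the mismatch itself. The exploratory label is given as a reason for not correcting for multiple tests; it does not make a paired test compare independent arms. The two-group tests in the preceding sentence are assigned to clinical and demographic variables, in a paragraph that lists neuropsychological data separately, so they do not fill the gap. This is also more than a detail left to a SAP, because the protocol names a test and a purpose that disagree.

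**Conclusion.** Wrong as written, of moderate severity. A paired t-test does not compare change between two independent, unmatched arms, and the protocol names no other between-arm test of cognitive change. On every literal way of carrying it out, the sentence gives either no test of the randomised comparison or an arbitrary one.

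The numerical consequence is conditional. If within-arm results are read as a group difference when exactly one arm is significant, the false-positive rate runs from about 6% to 50% for common changes between 0 and 0.8 SD, with its peak near 0.4 SD, against about 5% for a two-sample test. This rests on about 25 completers per arm, two-sided tests at 0.05 and the same true change in both arms.

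The defect is confined to the cognitive analyses. It still matters because the protocol says the study will inform on the cognitive effects of stopping estrogen, and because these results are to be read alongside the metabolic changes.

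**What to change.** Replace the sentence in Data Analysis with:

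> Change from baseline to year 2 in neuropsychological scores will be compared between the randomised groups by a two-sample t-test on change or, preferably, by ANCOVA of the year-2 score adjusted for baseline; within-arm paired t-tests are descriptive only.

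The two-sample test is the minimum that repairs the error; ANCOVA is a preference. The stated purpose of relating cognitive to metabolic change can stay. The cost is wording only: the same data, visits and software serve, and the sample size of 50 already fits a two-group comparison.

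### The arm-level tests named for relating cognitive change to PET change cannot show whether the two changes occur in the same women; one within-woman regression on data already collected would address this.

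*Protocol*

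**What the plan says.** The Data Analysis section of the protocol sets out two separate strands.

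- **PET.** A voxel-wise t-statistic is used "to identify the profile of voxels that significantly differed between subject groups". Twelve a priori regions (left and right) get a Bonferroni-type correction at 0.05.
- **Cognition.** Paired t-tests are applied to change in neuropsychological performance by randomised group. Their stated purpose is "to allow for consideration of correspondence with regional cerebral metabolism changes". They are run at 0.05 each, uncorrected, and described as exploratory.

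No correlation, regression or other analysis that uses both of a woman's changes together appears anywhere in the protocol. The data for one will exist. Under Subject Participation the baseline assessments include PET and the neuropsychological battery, and "All tests performed at baseline will be repeated at a 2-year follow-up". The paragraph on the importance of the knowledge to be gained gives the aim as "identifying changes in brain metabolism and cognitive function, which may result from discontinuation of estrogen use".

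**The concern.** The protocol states a purpose, correspondence between cognitive and metabolic change, and names for it only tests of arm-level change in each measure separately. Correspondence in the sense most readers would want is a statement about individuals: do the women who lose regional metabolism also lose performance? Two arm-level results placed side by side do not address that.

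The gap runs in both directions. If estrogen moves both measures through unrelated routes, both arm comparisons can be positive with no link within women. If there is a real link within women, it stays unseen unless it also moves both arm means far enough to be significant.

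The paired t-tests named in the same sentence raise a different question, since a paired test assesses change within an arm and does not compare arms. Replacing them with a two-sample test of change would not settle the present point, because correspondence would still be untested.

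At stake is a secondary interpretation: whether a metabolic finding can be described as tied to cognitive function.

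**Working it through.** **1. The plan's own figure.** Subject Recruitment says "we will need to retain 50 subjects to achieve the effect size of 0.80" and "we expect to randomize approximately 71 subjects who meet full inclusion criteria", with 30% attrition. Alpha, power and allocation ratio are not stated. I assume two-sided 0.05, 80% power and 1:1.

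- n per arm = 2(1.960 + 0.842)² / 0.80² = 2 × 7.85 / 0.64 = 24.5, so 25 per arm and 50 in total. A t-based calculation gives 25.5 per arm, and 79.1% power with 25.
- 50 / (1 − 0.30) = 71.4 randomised.

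The sample size reproduces and is not in dispute. I use 25 completers per arm below.

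**2. What the arm tests contain.** Write each woman's standardised 2-year changes as

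- metabolism: ΔM = −δM × arm + e
- cognition: ΔC = −δC × arm + f, with corr(e, f) = r within arm.

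The PET comparison estimates δM and a comparison of cognitive change estimates δC. The correlation r enters neither estimate nor either standard error. A regression of ΔC on ΔM with arm in the model tests r directly.

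**3. Illustration.** Assumed: normal changes, one region, PET at 0.05/12 = 0.0042, and a two-sample test of cognitive change at 0.05 (kinder to the plan than a paired test). "Both significant" is my yardstick for side-by-side agreement; the protocol does not state it.

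*No within-woman link, 0.8 SD arm effect on both measures.* Power is 0.4375 for PET at 0.0042 and 0.791 for cognition at 0.05. With r = 0 the tests are independent, so both are significant in 0.4375 × 0.791 = 0.346, about 35% of trials (simulation: 34% to 35%). The slope test rejects in 5% at the 0.05 level, its nominal rate.

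*0.8 SD arm effect on PET, cognition moved only through the link (δC = 0.8r).* A Fisher approximation for the slope test uses z = atanh(r) × √(50 − 1 − 3) = atanh(r) × 6.782, against a critical value of 2.865 at 0.0042:

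| r | z | Φ(z − 2.865) | Slope power, simulated | Both group tests significant, simulated |
|---|---|---|---|---|
| 0.5 | 3.726 | 0.80 | 81% | 19% |
| 0.4 | 2.873 | 0.50 | 51% | 14% |
| 0.3 | 2.099 | 0.22 | 23% | 8% |
| 0.2 | 1.375 | 0.07 | 6% | 5% |

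Simulated figures vary by about one percentage point between runs. Without the 12-region correction, slope power at r = 0.5 and 0.4 is 96% and 82%. The corrected column is the fair comparison.

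*r = 0.5, no arm effect on either measure.* Both group tests are significant in about 0.1% of trials; the corrected slope is detected in about 81%. This shows what the tests respond to. An association independent of treatment is not the trial's main question.

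**4. Limits on the gain.**

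- *Several scores.* The battery has about 11 measures and no composite. Testing all of them in 12 regions makes 11 × 12 = 132 slopes. At 0.05/132, power falls to about 57% at r = 0.5 and 25% at r = 0.4.
- *Selective loss.* The Data and Safety Monitoring paragraph removes women whose cognitive performance worsens. If, as an assumption, the worst 10% to 30% on cognitive change were missing at 2 years, r = 0.40 would shrink to about 0.35 to 0.29.
- *Adjustment.* The illustration adjusts for arm only. The two baseline values cost two further degrees of freedom.

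**The case against.** The strongest reply has five parts.

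- **No rule is stated.** A reader might infer that correspondence will be declared whenever both group tests are significant. The text says only that the cognitive tests allow correspondence to be considered. This stands: joint significance is an illustrative yardstick, not the plan's criterion.
- **A group-level correspondence can be real.** A reader might infer that the plan would report a correspondence that does not exist. If discontinuation truly shifts both measures, the arms do correspond at group level, and the stated aim concerns effects of discontinuation. This stands too. The error would lie only in carrying the result over to individual women, which the protocol does not expressly do.
- **The analysis is exploratory.** The main PET hypothesis is untouched, so the consequence is confined to secondary interpretation. This stands and limits the weight of the point. But the exploratory label excuses the missing multiplicity correction; it does not make tests of arm-level change informative about covariation.
- **A within-woman analysis may be in the analysis plan.** That plan is not shown, and nothing in the protocol excludes such an analysis. This stands in part. The point is not that detail is missing: the protocol gives a purpose and attaches to it a method that cannot serve the within-woman reading.
- **The regression is no cure-all.** The slope is not randomised evidence, is open to confounding, and has little power for weak links or across the whole battery. This stands. The slope should therefore be added to the arm comparisons, not treated as the sole evidence of correspondence.

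**Conclusion.** The point holds in limited form. The only methods the protocol names for considering correspondence are arm-level, and they can neither establish nor exclude a link within women. A better-matched analysis is available on the same completers.

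Under the stated assumptions, side-by-side agreement appears in about 35% of trials with no within-woman link. With a link of r = 0.4 to 0.5 it appears in only 14% to 19%, where a region-corrected slope has 51% to 81% power. At r = 0.2 the two approaches are about equally weak (6% against 5%). The documents supply the 0.80 effect size, the 50 completers and the 12 regions. Its use as the PET arm effect, the correlations, the 1:1 allocation and the normal changes are assumptions.

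The documents do not support the stronger readings that the plan fixes a flawed decision rule, that agreement between two real arm effects is spurious, or that the main PET conclusion is compromised.

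**What to change.** Add one paragraph to the Data Analysis section:

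- Name in advance one cognitive score, or a composite or small named set.
- For each of the 12 a priori regions, regress the woman's 2-year change in that score on her 2-year change in normalised regional FDG, with arm and both baseline values in the model.
- Report the slope with its 95% CI. Apply the 12-region correction, extended over all scores if more than one is tested.
- Keep the arm comparisons as the evidence on treatment effects, and describe any agreement between them as descriptive only.
- Describe the slope as an association, not as mediation.
- Report how many women lack 2-year data because of cognitive worsening, since their absence could weaken the slope.

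The cost is the paragraph and one regression per region and score. No new data, visits or participants are needed. A null slope should not be read as absence of a link, given the low power below about r = 0.4.
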